### Intervention fidelity

Intervention fidelity will be ensured through regular training of the research team who will use a standardised program to ensure that all subjects in the ILI receive uniform education, training and intervention. The delivery of the intervention will be assessed through regular observation.

### Case report forms and data entry

Subjects will be asked for permission to obtain their clinical information from their electronic medical records. Paper case report forms (CRFs) will be completed for each visit. Each CRF will be validated by a research investigator. The CRF data will be translated into electronic data. All data will be double entered into a secure electronic database in preparation for data analysis.

### Sample size calculations

The sample size is based on the number of subjects needed to provide a power equal to 0.8 to test the primary hypothesis at the 0.05 significance level. The primary outcome for the proposed study is weight loss at 12 months. We anticipate that the weight loss will be 7% higher in the lifestyle group compared to the usual care group at 12 months. The Look AHEAD study yields a conservative estimate of the standard deviation of percentage of weight loss across various populations to be 9%. Using ANCOVA method to calculate the sample size and with 30% inflation for dropouts, 69 subjects per group are needed for the primary outcome. Regarding glycaemic control, Unick et al. found a − 0.643 (± 0.99) % change [81]; however, a change of 0.5% is considered to be clinically significant and comparable to changes achieved with most diabetes medications. The 69 subjects per group is also sufficient to detect a 0.5% change in HbA1c (assuming SD = 1%; the same power, significant level, and dropout rate). The study will therefore aim to recruit a total of 138 subjects (69 per group) including a 30% dropout.

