**Methods:**

The planned study is an ongoing, non-blinded, pragmatic, randomised controlled, parallel-group trial examining the impact of an LED-based ILI on body weight and diabetes remission in younger (18–50 years) T2DM individuals with early diabetes (≤ 3-year duration). The ILI will be compared to usual medical care (UMC). The primary outcome will be weight loss at 12 months. Other key outcomes of interest include diabetes remission, glycaemic control, diabetes complications, cardiovascular health, physical activity, mental health, and quality of life. It is planned for the study to include 138 subjects for assessment of the primary outcome. Safety will be assessed throughout.

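### The 69 per group does not follow from the stated primary-outcome inputs, which need about 35 to 39 recruited; the claim that 69 also suffices for HbA1c is conditional on assumptions not given

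*Protocol article*

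**What the plan says.** All figures are in the protocol article under Sample size calculations. The size is meant to give "a power equal to 0.8 to test the primary hypothesis at the 0.05 significance level". The endpoint is fixed: "The primary outcome for the proposed study is weight loss at 12 months". The effect is "We anticipate that the weight loss will be 7% higher in the lifestyle group compared to the usual care group at 12 months", and the Look AHEAD study is cited for a "standard deviation of percentage of weight loss across various populations to be 9" per cent. The section names an ANCOVA method without a baseline correlation and concludes that "with 30% inflation for dropouts, 69 subjects per group are needed for the primary outcome".

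It then turns to glycaemic control. It cites a published HbA1c change of −0.643 (± 0.99) % and adds: "The 69 subjects per group is also sufficient to detect a 0.5% change in HbA1c", assuming SD 1% and the same power, significance level and dropout. The recruitment target is 138 in total, with the 30% dropout included.

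The Data analysis section specifies ANCOVA with the baseline value as covariate for both weight and HbA1c. The abstract says "It is planned for the study to include 138 subjects for assessment of the primary outcome".

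**The concern.** The primary-outcome inputs describe a large standardised effect, 7/9 = 0.78, which needs only a small trial. The HbA1c inputs describe a much smaller one, 0.5/1 = 0.50. The same recruitment figure cannot be the number needed for 80% power on the first and, without further assumptions, also be enough for the second.

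Two things are at stake. This paragraph is the only justification in the article for the number enrolled, and a reader who checks it will not recover the figure. A non-significant HbA1c result might also be read as coming from a comparison with 80% power, when that power depends on assumptions the reader cannot see.

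**Working it through.** **Inputs from Sample size calculations.** Power 0.80; alpha 0.05; weight difference 7, SD 9; HbA1c difference 0.5, SD 1; dropout 30%; 69 per group. Allocation is 1:1 (Randomisation and allocation concealment). Sidedness is not stated, so two-sided is assumed.

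**1. Can 69 be reproduced for weight?** Unadjusted, n per group = 2(1.96 + 0.8416)² (SD/difference)².
- 2 × 7.849 × (9/7)² = 25.95. The t-based value is 26.9, so 27 evaluable.
- Dropout as division by 0.7: 27/0.7 = 38.6, so 39 recruited.
- Dropout as multiplication by 1.3: 27 × 1.3 = 35.1.

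Other routes also fall short of 69:
- One-sided alpha: 31–32 after division by 0.7.
- Power 0.90: 50–52. Power 0.95: 62–63.
- Adding the 10% early replacement (Subject replacement section) to 26/0.7: about 41.

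**2. Can ANCOVA raise the number?** No. Let ρ be the baseline-to-12-month correlation. If the SD is that of a single time point, the variance is multiplied by (1 − ρ²). If it is the SD of change, with equal variances at the two times, the factor is (1 + ρ)/2. Neither exceeds 1, so an undisclosed correlation cannot lift 39 to 69.

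**3. What does 69 give for weight?** 69 × 0.7 = 48.3, about 48 evaluable per group.
- Unadjusted t-test power for 7 with SD 9: 0.965.
- Difference detectable with 80% power: 5.2 points (normal approximation: 2.8016 × 9 × √(2/48) = 5.15).
- For 48 per group to give only 80% power at a difference of 7, the SD would have to be about 12.2%.

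**4. Is 69 sufficient for HbA1c?** Unadjusted, 2 × 7.849 × (1/0.5)² = 62.8 (t-based 63.8), so 63–64 evaluable. That is 90–92 recruited after division by 0.7, or 82–84 after multiplication by 1.3. At 48 per group, unadjusted power is 0.68.

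With ANCOVA at 48 per group, power depends on what SD 1% refers to:

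| ρ | SD of HbA1c at one time point | SD of change |
|---|---|---|
| 0 | 0.68 | 0.93 |
| 0.3 | 0.72 | 0.85 |
| 0.5 | 0.80 | 0.80 |
| 0.7 | 0.92 | 0.75 |
| 0.8 | 0.98 | 0.72 |

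The columns meet at ρ = 0.5 because 1 − 0.25 = (1 + 0.5)/2 = 0.75. So 80% power requires ρ of at least about 0.5 on the first reading and at most about 0.5 on the second. If inflation means multiplying by 1.3, then 69/1.3 = 53 evaluable, and the limits become at least about 0.4 and at most about 0.65.

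**The case against.** The strongest reply is that nothing harmful follows. The primary analysis has more power than claimed, HbA1c is listed under Secondary objectives, and a condensed article may leave a correlation to the full protocol. Most of this stands. The weight analysis is not at risk, and omitting the correlation is not itself the fault. But the omission cannot explain the primary figure, since no correlation raises 39 to 69. The section also asserts sufficiency for HbA1c as a plain fact.

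Three stronger readings are tempting, and the documents do not support them.
- A reader might infer that HbA1c set the 69, because 47.1 rounded up to 48 and divided by 0.7 gives 68.6, so 69, at ρ = 0.5. The match is suggestive, but the article does not say so, and ρ = 0.4 on the single-time-point reading with multiplication by 1.3 also gives 69.
- A reader might say that HbA1c power lies between 0.68 and 0.80 for correlations from 0 to 0.5. That holds only if SD 1% is a single-time-point SD. The section cites the spread of a change just before, which makes the SD-of-change reading at least as natural, and there a lower correlation helps.
- A reader might see a contradiction in the abstract, since 138 × 0.7 is about 97 evaluable. Its wording can equally mean enrolling 138 in order to assess the outcome.

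Sidedness also matters at the margin. A one-sided test with multiplication by 1.3 would need 65–67 for HbA1c with no correlation, but no one-sided test is stated.

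**Conclusion.** The point holds in two parts. First, 69 per group is not the number needed for 80% power on the primary outcome. The stated inputs need about 27 evaluable per group, so 69 is about 1.8 times the 39 that would have to be recruited (69/39 = 1.77). After 30% dropout, primary power is at least 0.96. This rests on a two-sided test and an SD of 9%; adjustment only strengthens it. The error favours the trial, so it is a wrong justification and not a power deficit.

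Second, sufficiency for HbA1c is conditional. It fails for an unadjusted comparison (0.68). With ANCOVA it holds or fails according to the correlation, the type of SD and the inflation convention. The documents do not show that HbA1c is underpowered, only that the unqualified statement is not established.

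Severity is minor to moderate. The recruitment target and the analysis need not change.

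**What to change.** Keep 138 and reword the Sample size calculations section:
- State that the primary outcome needs about 27 evaluable per group (up to 39 recruited with 30% dropout), and that 69 recruited gives power of at least 0.96 after dropout.
- Have the sponsor name the calculation that actually produced 69, with the type of SD, the assumed baseline correlation, sidedness, and whether dropout was applied by dividing by 0.7 or multiplying by 1.3. These should come from the sponsor's records and not be back-fitted to the number.
- State HbA1c power as conditional on those assumptions, with the unadjusted 0.68 at 48 per group for reference.
- Optionally, say in the abstract that 138 is the number recruited.

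The cost is wording only, with no extra subjects. The HbA1c claim becomes conditional.

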### Subject replacement

Any subject who drops out or is withdrawn in the first 6 weeks of study participation will be replaced. We estimate about 10% of recruited participants will be in this category.

### Randomisation and allocation concealment

Consented eligible subject will be randomly allocated to either receive intensive lifestyle intervention or usual medical care. Allocation will be made in a 1:1 ratio via a web-based system that uses a computer-generated randomisation list with variable block sizes (2, 4, and 8). The allocations are computer generated in Stata (version 13.1) by the trial statistician and programmed into an online randomisation service (https://www.sealedenvelope.com/) to which the trial coordinating team and investigators have no access.

When the subject has been recruited to the study, the subject will be allocated a study number, given sequentially; starting at one and the subject’s baseline data will be collected. Once this has occurred, only the person recruiting the subject will be informed of the group that has been randomly assigned to that study number. If a subject drops out of the study, the assigned study number will not be reused.

### Data analysis

Once all data are entered, multi-item scales will be computed and the univariate distributions of all outcome measures and potential covariates and confounders will be examined. If out-of-range values are found, we will attempt to determine the correct value or, failing this, the value will be treated as missing. Data will be expressed as frequencies and percentages for categorical variables, mean and (±) standard deviation for continuous variables or as median accompanied by interquartile range (IQR) for skewed continuous variables, as appropriate. Depending on the distribution of the data, independent student t-tests or Mann-Whitney U tests will be used to compare outcomes between the groups. Categorical baseline characteristics were compared using Chi squared tests. It is anticipated that some measures will exhibit substantial positive skew, and for these, we will determine if a logarithmic or power (e.g. Box-Cox) transformation is able to reduce the deviations from normality for those analyses involving the continuous version of the variable.

The main objective of the proposed study is to examine the effectiveness of an ILI. The ILI will be compared to usual care. The study will examine the primary outcome of weight loss, and also focus on improvement in glycaemic control. This will be assessed using an ANCOVA model. The first response variable will be weight at one year. The covariates will be weight at baseline and a binary variable indicating whether the subject was in the intervention group or the usual group. The regression coefficient of the group term represents the effect size of the intervention. In addition to this unadjusted analysis, an adjusted analysis will also be performed by adding body fat, fat free mass, HbA1c, and medication as covariates in the model. Similar unadjusted and adjusted ANCOVA models to assess glycaemic control using HbA1c will be fit. The primary analyses will be done using the intention-to-treat (ITT) method. Secondary outcomes (body composition and weight loss maintenance, insulin sensitivity/resistance, cardiovascular health and risk, impact on diabetes complications and liver function, changes in physical activity, mood, and quality of life) will be analysed in the same way, using unadjusted and adjusted analyses, under the ITT principle. Continuous measures will be analysed using an ANCOVA model and categorical outcomes using the appropriate generalised linear model, with the baseline measure of the outcome as a covariate. All outcome measures will also be analysed with per protocol.

In case of missing values, data imputation as well as comparison between imputed and non-imputed scores will be undertaken. A macro will be written that, for each measure, 1) identifies each pattern of missing data that occurs for the items used to construct the measures, 2) performs a separate regression analysis for each pattern predicting the measure value, for those with complete data, from the non-missing items for that pattern, and 3) uses the regression equation to replace the missing measure value with the regression-based predicted score for people having that pattern of missing data. Missing data are only replaced with predicted scores when the regression analysis indicates that the predicted score is a good estimate (i.e., when R-squared > 75% for the regression equation; almost always the case except for those who are missing more than 50% of items). Subgroup analysis will be performed gender and baseline BMI (< 30 and > = 30 kg/m^2^).

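### The data analysis section names two between-group tests for the same continuous outcomes: a t-test or Mann-Whitney test chosen from the data, and a baseline-adjusted ANCOVA

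*Protocol article*

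**What the plan says.** All references are to the protocol article.

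- **Data analysis, first paragraph.** After data screening and descriptive statistics: "Depending on the distribution of the data, independent student t-tests or Mann-Whitney U tests will be used to compare outcomes between the groups". The next sentence deals with categorical baseline characteristics. A log or Box-Cox transformation is foreseen for skewed measures.
- **Data analysis, second paragraph.** Weight loss and glycaemic control are assessed by ANCOVA: "The first response variable will be weight at one year", with baseline weight and group as covariates and the group coefficient as the effect. Other continuous outcomes follow the same model with their own baseline value. An additional adjusted analysis is formed by "adding body fat, fat free mass, HbA1c, and medication as covariates in the model".
- **Sample size calculations.** "The primary outcome for the proposed study is weight loss at 12 months". The trial is sized by an ANCOVA method to "provide a power equal to 0.8 to test the primary hypothesis at the 0.05 significance level". The inputs are a 7% difference and a "conservative estimate of the standard deviation of percentage of weight loss across various populations to be 9" (per cent).
- **Study design.** The trial is open-label. Table 1 lists a single scale as the source of body weight and bioimpedance body composition, and does not give the unit of body fat.

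**The concern.** The two paragraphs assign different tests to the same outcomes. The first lets the observed distribution choose between two tests and uses no baseline covariate. The second fixes a baseline-adjusted model. A reader holding both could report whichever gives the smaller p-value and point to the protocol either way. In an open-label trial the between-group test should be beyond dispute before the data are seen.

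Two smaller matters belong to the same text. The effect and SD used for sizing are in percent loss, while the ANCOVA coefficient is in units of weight. The adjusted model adds body fat and fat-free mass to a model that already holds baseline weight, and these three overlap.

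**Working it through.** **1. The plan's own figure.** With two-sided 0.05 (sidedness is not stated), power 0.80, difference 7 and SD 9:

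n = 2 × (1.960 + 0.842)² × (9/7)² ≈ 26 per group; 26 / 0.70 gives 38 with dropout.

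The stated 69 is not reproduced from the weight inputs. It is matched by the HbA1c inputs (0.5, SD 1) if a baseline correlation of 0.5 is assumed: 48 / 0.70 ≈ 69. That is a separate matter. What is used here is the number of completers: 69 × 0.70 ≈ 48 per group.

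**2. Assumptions for the comparison of tests.** From the article: 7% effect, SD 9%, 48 per group. Assumed, because the article gives no baseline weights: mean 100 kg, SD 12, 16 or 20 kg, normal data, percent loss independent of baseline weight.

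**3. Power.** For a two-sample test, power ≈ Φ(δ / (σ√(2/n)) − 1.96), with √(2/48) = 0.204. For raw 12-month weight, σ ≈ √(baseline SD² + 9²) kg at a mean of 100 kg, and δ = 7 kg.

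| Baseline SD (kg) | σ of 12-month weight (kg) | Formula: raw weight | Simulated t-test, raw weight | Simulated ANCOVA | Simulated t-test, percent loss |
|---|---|---|---|---|---|
| 12 | √(144 + 81) = 15.0 | 0.63 | 0.64 | 0.96 | 0.96 |
| 16 | √(256 + 81) = 18.4 | 0.46 | 0.47 | 0.96 | 0.96 |
| 20 | √(400 + 81) = 21.9 | 0.35 | 0.35 | 0.95 | 0.96 |

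Mann-Whitney on raw weight is similar (0.62, 0.46, 0.34). For percent loss the formula gives Φ(7 / (9 × 0.204) − 1.96) = 0.97. The loss of power therefore depends wholly on the scale to which the unadjusted test is applied, and the sentence does not name a scale.

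**4. Type I error.** Each test alone holds its level. Choosing between t-test and Mann-Whitney by a normality check also stays near 0.05 (0.045 to 0.061 at 48 per group). The inflation comes from having both an unadjusted test and ANCOVA. If significance on either a raw-weight t-test or ANCOVA counts, the simulated error is about 0.09, and about 0.10 with Mann-Whitney as a third option. As a yardstick, two independent tests would give 1 − 0.95² = 0.0975. If the unadjusted test is on percent loss, it nearly coincides with ANCOVA and the inflation is slight.

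**5. Scale.** 7% is 0.07 × 80 = 5.6 kg at 80 kg and 0.07 × 120 = 8.4 kg at 120 kg (assumed weights). A coefficient in weight units cannot be set directly against the 7% target. The cost in power is almost nil (0.95 to 0.96 against 0.96).

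**6. Covariates of the adjusted model.** If body fat is in kg, weight = fat + fat-free mass, and the matrix (intercept, weight, group, fat, fat-free mass) has rank 4 of 5. In a simulated data set of 96 subjects the group coefficient was −8.59 whichever redundant column was dropped. If body fat is in percent, the matrix has full rank, with variance inflation factors of about 71 (weight), 36 (percent fat) and 118 (fat-free mass) under assumed distributions. These fall on the nuisance covariates.

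**The case against.** The strongest reply is that the plan does name its primary analysis. The second paragraph specifies the response, the covariates and the effect for weight, extends ANCOVA to all continuous measures, and agrees with the sizing method. The t-test sentence stands among screening and descriptive steps and is followed by one on baseline characteristics, so it may have been meant descriptively. This largely stands. A reader might infer that the primary test is undetermined; the documents do not support that. But the sentence speaks of outcomes, and baseline characteristics get their own sentence, so the literal conflict remains.

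Other stronger readings also fail:

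- **The unadjusted test discards most of the power.** This is true only for raw 12-month weight. The outcome is defined as weight loss, and a t-test on percent loss has about the same power as ANCOVA.
- **The ANCOVA does not estimate weight loss.** With baseline weight in the model, the group coefficient for 12-month weight equals that for change in weight apart from sign. Only the unit differs from the sizing.
- **The adjusted model cannot be fitted.** Exact redundancy needs fat in kg, and even then dropping one column leaves the group effect unchanged.
- **Post-randomisation medication would be adjusted for.** The article gives no time point. Baseline is the natural reading beside the other covariates, and an analysis plan would settle it.

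**Conclusion.** The point holds as a conflict in wording. The first paragraph of the Data analysis section prescribes a data-chosen, unadjusted test for outcomes that the second paragraph assigns to a baseline-adjusted ANCOVA. ANCOVA is the probable primary analysis, and its power for the stated 7% and SD 9% is not in doubt (about 0.96 at 48 per group).

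The size is a worst case: type I error of about 0.08 to 0.10 instead of 0.05 if either result could be claimed, and power of about 0.35 to 0.63 if the unadjusted test were run on raw weight. Both rest on the assumed baseline weights and normal data. Neither applies to any material extent if the unadjusted test is on percent loss.

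The scale mismatch concerns how the result is stated and read, not power. The covariate redundancy is confined to the supplementary adjusted model and does not alter the group effect.

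**What to change.** 1. Limit the t-test and Mann-Whitney sentence to baseline or descriptive comparisons, or delete it for outcomes.
2. State once that the baseline-adjusted ANCOVA is the only between-group test for continuous outcomes, with a transformation or robust standard errors if residuals are skewed.
3. Minor: restate the 7% and SD 9% on the analysed scale, or report percent loss as a supportive result.
4. Minor: in the adjusted model keep only one of body fat and fat-free mass beside baseline weight.

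All four are changes of wording. They need no further data or participants, and should be made before outcome data are analysed.

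### The only stated imputation rule cannot fill a missed 12-month weight or HbA1c, so the intention-to-treat ANCOVA would run on about 48 of 69 subjects per arm

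*Protocol article*

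**What the plan says.** All references are to the protocol article.

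- **Primary analysis (Data analysis).** An ANCOVA with baseline weight and arm as covariates: "The first response variable will be weight at one year". HbA1c is handled in the same way. The primary analyses are to follow intention-to-treat.
- **Missing data (Data analysis).** The section promises imputation in general terms and a comparison of imputed with non-imputed scores. The only method it describes is a macro, run for every measure. The macro sorts subjects by which items of a measure are missing, regresses the measure on the remaining items among subjects with complete data, and then "uses the regression equation to replace the missing measure value with the regression-based predicted score for people having that pattern of missing data". There is a gate: "Missing data are only replaced with predicted scores when the regression analysis indicates that the predicted score is a good estimate", defined as R-squared above 75%.
- **Expected loss (Sample size calculations).** 69 per group, "including a 30% dropout".
- **After withdrawal (Subject adherence, withdrawal, safety measures and adverse events).** Assessments and data collection stop, and data already collected are kept for use. Inability to adhere to the protocol is itself a ground for withdrawal.
- **Nature of the outcomes (Table 1).** Weight is a scale reading and HbA1c a central-laboratory value. Neither is built from items.

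**The concern.** The rule is written for questionnaires. It can rebuild a scale score when some answers are missing. It has no input when the whole visit is missing, and for weight and HbA1c a missing value is always wholly missing. Followed as written, the plan therefore imputes nothing for its primary outcome and analyses completers under an intention-to-treat label.

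A completers' ANCOVA is valid if dropout depends only on arm and baseline weight. That is doubtful here. Only the lifestyle arm carries the diet and exercise demands, and subjects who cannot adhere are withdrawn and no longer measured. If those who leave are the ones losing less weight, the completers' estimate is too favourable.

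**Working it through.** **1. How many subjects are left.** The plan's inputs for the primary outcome are: "We anticipate that the weight loss will be 7% higher in the lifestyle group compared to the usual care group at 12 months"; a "standard deviation of percentage of weight loss across various populations to be 9" percent; and a sample size "to provide a power equal to 0.8 to test the primary hypothesis at the 0.05 significance level" (two-sided assumed).

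- Weight: n = 2 × (1.96 + 0.84)² × 9² / 7² ≈ 26 per group; 26 / 0.7 gives 38. The plan states: "Using ANCOVA method to calculate the sample size and with 30% inflation for dropouts, 69 subjects per group are needed for the primary outcome". The weight inputs do not give 69.
- HbA1c (difference 0.5, SD 1): n ≈ 63. With an ANCOVA factor 1 − r² and an unstated r = 0.5, 63 becomes 48, and 48 / 0.7 gives 69. So 69 fits the HbA1c aim under an assumed r. This does not affect the present point.
- Either way, 69 × 0.7 ≈ 48 per arm are expected to have a 12-month value.

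**2. Power with completers only.** SE = 9 × √(2/48) = 1.84; 7 / 1.84 = 3.81; power = Φ(3.81 − 1.96) ≈ 0.968. Precision is not the problem.

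**3. Bias with completers only.** Simulation with 69 per arm, effect −7, residual SD 9 (the plan's percentages carried over as kilograms) and assumed baseline SD 18 kg.

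| Dropout | True effect, all randomised | Completers' estimate | Type I error if no effect |
|---|---|---|---|
| 30% at random in each arm | −7.0 | −7.0 (model SE 1.84, true 1.83 to 1.88) | 4.6% |
| Lifestyle arm: logit of dropout = −0.95 + 0.8 × residual/9 (about 30%); usual care: 30% at random | −7.0 | −8.9 | 18% |

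The second row overstates the effect by 1.9, or 1.9 / 7 ≈ 27%. A variant in which lifestyle dropout depends on interim weight change gave −9.1 and about 20% type I error. Using the interim weight removed that bias.

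**4. Could the rule be stretched to baseline weight?** The text does not say so, because baseline weight is not an item of 12-month weight. If someone tried it:

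- The gate: with slope 1 and residual SD 9, R² = s² / (s² + 81). For an assumed baseline SD s of 12 to 22 kg this is 0.64 to 0.86, so the 75% gate might or might not open.
- Arm in the equation: the estimate stays at −7.0, but the model SE is about 1.27 against a true 1.83 (ratio 0.69). Filled-in points carry no residual and are counted as data: √0.7 × √(48/69) ≈ 0.70. Type I error = 2 × [1 − Φ(1.96 × 0.7)] = 17%; simulated 18%.
- Arm omitted: the estimate shrinks to 0.7 × (−7) = −4.9, and type I error stays near 4.5%.

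These two harms are alternatives and do not add up.

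**5. Where the rule fits.** A seven-item scale with one, two or three items missing in 30% of subjects, arms pooled: R² is 0.98, 0.95 and 0.92. The effect falls from 2.44 to 2.42, 2.47 to 2.43 and 2.43 to 2.37 (about 1 to 2.5%). The ratio of model SE to true SE is 0.98 to 1.04. The harm is negligible.

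**The case against.** **The article condenses a fuller protocol.** It commits generally to imputation, and the handling of wholly missing visits is commonly left to an analysis plan. That would answer a complaint about silence. But the article states a specific rule, applies it to every measure and names no other. The promised comparison of imputed with non-imputed scores cannot help where nothing can be imputed.

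**Completers need not be biased.** This stands: the first row of the table shows a correct estimate and test when dropout is unrelated to response given arm and baseline weight. The −8.9 is an illustration of size and not a forecast.

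**A reader might infer that a true 7 will be reported as 10.** That is 7 / 0.7, which needs every lifestyle dropout to lose all benefit; with half kept it is 7 / 0.85 = 8.2. Nothing in the article supports either assumption. Multiple imputation from baseline weight alone would not repair that case, since it also returns about −10.0. This is why interim weights and a sensitivity analysis are needed.

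**A reader might also infer that the plan's tests have 17% type I error or a 30% shrunken effect.** Those figures belong to imputing 12-month weight from baseline weight, which the article does not state. Nor does it state fitting by arm. For partly answered questionnaires, a type I error of about 7% arises only with R-squared at the 75% floor, 30% of subjects affected and fitting by arm.

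**The 30% is a planning figure.** Dropouts in the first 6 weeks (estimated at about 10%) are replaced, and whether they count within the 30% is not stated. Permission is sought to use clinical records, so a missed visit without withdrawal need not lose the weight. Actual loss may be smaller than 30%.

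**Conclusion.** The point holds for single-reading outcomes, above all the primary one. The stated rule cannot impute a wholly missed 12-month weight or HbA1c. At the planned dropout, the analysis labelled intention-to-treat would rest on about 48 of 69 subjects per arm. Bias follows only if dropout relates to weight response beyond baseline weight and arm. The withdrawal rule for non-adherence makes that plausible, but the article gives no figures from which its size could be known. If poorer lifestyle responders leave more often, the illustrative size is about −9 for a true −7, with type I error of 18 to 20%. These results rest on 30% loss, residual SD 9, an assumed baseline SD of 18 kg and the assumed dropout model. Power is not at issue, and neither is the use of the rule for partly completed questionnaires.

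**What to change.** For 12-month weight and HbA1c, replace the item-based rule with one of these:

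- a linear mixed model for repeated measures (arm by visit, baseline value as covariate) that includes every randomised subject and all scheduled values already collected; or
- multiple imputation by arm, with the interim values among the predictors, combined by Rubin's rules.

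Both need the outcome recorded at comparable visits in the two arms; the three-monthly visits are the natural choice, if it is recorded there. Both also assume that data are missing at random given what was observed. Add one sensitivity analysis in which lifestyle dropouts follow the usual-care course, to cover benefit lost after the last measurement.

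Limit the macro to partly completed questionnaires, where it and its R-squared gate may stay as written. State that it is not to be extended to single readings by predicting from baseline.

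The cost is a change of analysis wording, some programming and possibly slightly wider intervals. No extra subjects or visits are needed.
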